Describe the prevalence of psychological distress and characteristics associated with poorer mental health. Hypotheses include:*Poorer mental health will be associated with demographic variables (including younger age, female sex, coming from Black, Asian, or other racial or ethnic minority groups*).*Poorer mental health will be associated with occupational characteristics (including role, pay grade, work setting, redeployment status*).Establish the true prevalence of mental disorders via diagnostic interviews.Secondary objectives include exploring the factors associated with poor mental health, patterns of reported distress over time, and qualitatively exploring experiences of staff support interventions. We will:Describe workplace factors associated with poorer mental health. Hypotheses include:*Poorer mental health will be associated with higher levels of reported moral injury*.*Poorer mental health will be associated with reported lack of access to PPE*.*Poorer mental health will be associated with perceived lack of support from leaders, team, friends/family*.Describe patterns and persistence of psychological distress symptoms over time. Hypotheses include:*Mental health and well-being will follow the trajectory of the pandemic, with poorer outcomes evident during/after higher levels of COVID-19 prevalence (eg, as measured by daily deaths, hospital admissions*).*Poorer mental health at baseline will be associated with poorer mental health at 6-month and 12-month follow-up points*.*Predictors of poorer mental health at follow-up time points will include younger age, female sex, racial or ethnic minority group, being a nurse, perceived lack of support, lack of access to PPE, and higher levels of reported moral injury*.Qualitatively evaluate tiered and tailored staff support programmes being implemented locally and nationally, using in-depth interviews and thematic analysis. This will enhance our understanding of how we could further scale up effective support programmes within and across Trusts.Provide a platform for further randomised controlled trials (RCTs), and observational or intervention studies, including:An ethnic inequalities module, which will explore ethnic inequalities in mental health and occupational outcomes across NHS staff and the mechanisms that perpetuate these inequalities, using a mixture of quantitative and qualitative data (Tackling Inequalities and Discrimination Experiences in health Services Study: TIDES https://tidesstudy.com).Estimation of parameters of interest which could be later incorporated when designing an RCT or a pragmatic trial, for example, prevalence of psychosocial distress, intraclass correlation coefficient across the NHS Trust.An RCT testing a well-being app for use by NHS staff.

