
## Methods

### Design and setting

This study consists of three main components:

A longitudinal cohort study, consisting of surveys administered at baseline, 6 months and 12 months, to track outcomes over time.A diagnostic interview study, using a clinical diagnostic measure to ascertain the true prevalence of mental disorders.A qualitative interview study, using semistructured interviews to explore experiences of using (or reasons for not using) staff support programmes.

The study will be carried out in 18 NHS Trusts in locations across England.

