##### Data collection

Baseline data were collected from April 2020 to January 2021. Staff completing the baseline survey will be invited to complete follow-up surveys at 6 months and 12 months after they have completed the baseline survey. All participants will be followed up at each subsequent data collection point, regardless of whether they completed the previous survey, unless they choose to withdraw from the study.

The online survey will be administered using Qualtrics survey software, hosted by King’s College London, and downloaded data will be pseudonymised and stored on secure servers at King’s College London and University College London.

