### Analysis plan

#### Longitudinal cohort study

Response weights will be calculated for each Trust, generated using a raking algorithm based on age, sex, ethnicity and role (using Trust population data obtained from Human Resources), with missing demographic data imputed using multiple imputation (for the purposes of weighting only). Trusts with response rates under 5% will be dropped from the analysis. Representativeness of the sample will be described using frequencies and percentages, and descriptive statistics given for each variable to summarise participants (frequencies and weighted percentages for categorical variables, mean and SD for continuous variables). We will examine differences between participants completing only the short survey, compared with those completing both the short and long surveys. We will summarise the weighted prevalence of the primary and secondary outcomes, stratified by sociodemographic and occupational factors. We will explore potential longitudinal associations between sociodemographic characteristics and occupational factors with the outcome measures (eg, GHQ-12, GAD-7, PHQ-9, AUDIT, PCL-6, MIES). Three-level random intercept linear or logistic (depending on the distribution of the outcome) regression models will be used to account for the hierarchical structure of the data, considering observations from baseline, 6-month follow-up and 12-month follow-up at level 2 and NHS trusts at level 3. We will use a measure of pressure on Trusts as the key exposure (eg, ratio of beds in use to staff numbers, ie, those not on sick leave), plotting levels of this exposure over time (aggregated at the Trust level), before partitioning the data into meaningful periods corresponding to burden level over the baseline data collection period (April 2020 to January 2021). We will plot all measures over time to look at patterns between this exposure and outcome levels, and use three-level random intercept logistic and linear regression models, as appropriate, to explore factors associated with outcomes in each period.

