## Ethical considerations

### Longitudinal cohort study

Once consented into the study, an automatically assigned ID number will be used for each participant, allowing survey data to be held pseudonymously. All study staff will adhere to relevant data protection regulations, and will maintain confidentiality at all times. No information that could identify any individual participant will be used in reports or publications, or passed on to the Trusts.

Participants will be able to stop the survey at any point, and can skip questions wherever desired. The only required questions are email address and main employing Trust. Signposting information will be provided for any participants who experience distress in answering survey questions (eg, links to websites for NHS front-line staff, Mind, Samaritans and the WHO resources for dealing with psychosocial considerations during the pandemic).

There might be some indirect benefits to the participant when taking part. People often value the opportunity to share their opinions, experiences and feelings, and several free-text options throughout the surveys offer the chance to do this.

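### The pooled-wave models put survey occasions at level 2 and specify no participant intercept, so as written the standard errors for time-fixed person-level predictors are too small

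*Protocol article*

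**What the plan says.** The Analysis plan (Longitudinal cohort study) specifies three-level random intercept models, linear or logistic according to the outcome. It assigns the units to levels as follows: "considering observations from baseline, 6-month follow-up and 12-month follow-up at level 2 and NHS trusts at level 3". Level 1 is not named, and the participant is not named as a clustering unit.

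Elsewhere the article describes a cohort and not repeated cross-sections:

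- Design and setting: "A longitudinal cohort study, consisting of surveys administered at baseline, 6 months and 12 months, to track outcomes over time".
- Study procedures, Data collection, on who is invited: "Staff completing the baseline survey will be invited to complete follow-up surveys at 6 months and 12 months". The same section on missed waves: "All participants will be followed up at each subsequent data collection point, regardless of whether they completed the previous survey".
- Ethical considerations, Longitudinal cohort study: "an automatically assigned ID number will be used for each participant", so the waves can be linked within a person.
- Aims, objectives and hypotheses: "Poorer mental health at baseline will be associated with poorer mental health at 6-month and 12-month follow-up points". The study itself expects correlation within a person.

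The same Aims section lists what is to be tested across waves: "Predictors of poorer mental health at follow-up time points will include younger age, female sex, racial or ethnic minority group, being a nurse". Support, PPE and moral injury complete that list.

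**The concern.** In this design occasions are nested in participants, and participants in Trusts. If occasions occupy level 2, the only place left for the person is level 1, beneath the occasion, where the person is merely the residual. A person's three answers then fall in three different level-2 units and share nothing but the Trust intercept. That model suits fresh samples of staff at each wave, not a followed cohort.

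Three answers from one person would be counted as three people's worth of information about that person's age, sex or ethnicity. Intervals for such predictors would be too narrow and associations declared too often. For change within a person the error runs the other way, because the model ignores the gain from comparing people with themselves.

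**Working it through.** The article gives no sample size, power or standard error for these models, so there is no figure of its own to reproduce. The size of the error has to be computed from assumptions.

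**Inputs.** From the article: up to m = 3 responses per person, 18 Trusts. Assumed, because the article gives no value: within-person correlation ρ = 0.3, 0.5 or 0.7.

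**Time-fixed predictors.** The true variance is 1 + (m − 1)ρ times the model's variance. The ratio of true to model standard error is the square root of that. The true type I error of a nominal 5% test is 2[1 − Φ(1.96/√(1 + (m − 1)ρ))].

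| m | ρ | Variance ratio | SE ratio | Type I error |
|---|---|---|---|---|
| 2 | 0.3 | 1.3 | 1.14 | 8.6% |
| 2 | 0.5 | 1.5 | 1.22 | 11.0% |
| 2 | 0.7 | 1.7 | 1.30 | 13.3% |
| 3 | 0.3 | 1.6 | 1.26 | 12.1% |
| 3 | 0.5 | 2.0 | 1.41 | 16.6% |
| 3 | 0.7 | 2.4 | 1.55 | 20.6% |

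**Check by simulation.** Setting: 18 Trusts, 40 participants per Trust, 3 waves, 2,000 runs, a continuous outcome and a null binary person-level covariate, fitted by generalised least squares with known variances. Assumed variances were 0.02 for Trust and 0.01 for Trust-by-wave out of a total of 1, with the remaining 0.97 split between person and residual in the ratio ρ to 1 − ρ.

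- As written (Trust and wave-within-Trust intercepts): type I error 12.2%, 16.5% and 19.9% at ρ = 0.3, 0.5 and 0.7.
- With a participant intercept added: 4.6%, 4.8% and 4.5%. The Monte Carlo standard error near 5% is √(0.05 × 0.95/2000) = 0.5 percentage points, so these agree with the nominal level.

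**Time-varying predictors.** The inflation is roughly 1 + (m − 1)ρxρy, where ρx is the predictor's own correlation between waves. With ρx = ρy = 0.5 (assumed) and m = 3 it is 1 + 2 × 0.25 = 1.5, and the type I error is about 11% instead of 17%. The 6-month survey asks again about support from colleagues and friends or family and repeats the moral injury scale, so these belong here. PPE access can also change between waves.

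**Uneven response.** People who answer once add no within-person correlation. If 70%, 20% and 10% answer once, twice and three times (assumed) and ρ = 0.4, then per 100 people there are 70 + 40 + 30 = 140 records. The average inflation is (70 × 1 + 40 × 1.4 + 30 × 1.8)/140 = 180/140 = 1.29, and the type I error is about 8%.

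**Within-person change.** With no Trust-by-wave variance, the true standard error is √(1 − ρ) = 0.84, 0.71 and 0.55 times the model's. But the model as written contains a wave-within-Trust intercept, which can dominate. With variance 0.01 for it, ρ = 0.5 and 500 respondents per Trust and wave (both assumed), and about 0.99 of variance left for person and residual, the modelled variance of a Trust-wave mean is 0.01 + 0.00198 = 0.01198. The relevant true value is about 0.01 + 0.00098 = 0.01098. The model's standard error is then √(0.01198/0.01098) = 1.04 times the true one.

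**Logistic models.** These figures are for linear outcomes. In the logistic case, leaving out the participant intercept also moves the odds ratio from a participant-specific towards a population-averaged meaning.

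**The case against.** The strongest reply is that the sentence is loosely worded. Level 1 is unnamed, the stated purpose is to respect the hierarchy of the data, and in an ID-linked cohort a three-level model would naturally mean occasion, participant, Trust. That may be what was intended, so the article does not show that the final standard errors will be wrong. It does show that an analyst who follows the text would fit a model without within-person correlation. Nor is this detail left to a fuller plan: the article chose to state the levels, and states them in a way that does not fit the design.

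A reader might infer that nearly all of the study's hypotheses are affected. The text does not support that. The demographic and occupational hypotheses under the primary objective can be tested at one wave, with one record per person. Support and moral injury vary over time and are affected less.

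A reader might also infer that change over time is estimated with badly overstated standard errors. That follows only if Trust-by-wave variance is negligible; otherwise the excess may be a few per cent.

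Finally, the plan describes these models as exploring associations and attaches no alpha or power to them. That is so, and it tempers the type I framing. The same defect can be read as coverage of nominal 95% intervals: about 87–91% with two responses each and 79–88% with three.

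**Conclusion.** The point holds for models that pool waves. As written they omit the participant intercept, and standard errors for time-fixed person-level predictors are too small. With ρ between 0.3 and 0.7, the true type I error at nominal 5% is about 9–13% with two responses each and 12–21% with three. These ranges rest on an assumed correlation, on everyone answering two or three times, and on a linear outcome. Where many people respond once the error can fall below them, to about 8% in the example above.

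The direction for time-fixed predictors does not depend on the assumed value, only on the correlation being positive, which the study itself hypothesises. Single-wave analyses are untouched. For within-person change the standard errors tend to be too large, by an amount the article does not allow one to fix and which may be small.

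**What to change.** Replace the description of the levels with: 'survey occasions (baseline, 6, 12 months) at level 1, participants at level 2 and NHS Trusts at level 3, with random intercepts for participant and Trust and survey wave as a fixed effect'.

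Add a Trust-by-wave random intercept if the data support it. Moving occasions to level 1 removes the wave-within-Trust intercept that the present wording implies. The plan's key exposure is pressure on Trusts, which varies by Trust and time. If outcomes also vary by Trust and wave beyond what the model explains, dropping that term would make intervals for wave contrasts and for this exposure too narrow.

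In the same edit, define the levels for the period-specific models over the baseline collection window (April 2020 to January 2021). They carry the three-level label too, but no levels are given for them.

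The cost is a short change of text, wider intervals for person-level predictors and slightly more model fitting. No new data are needed, since participants already have an ID.

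### The Trust-pressure analysis stops its burden periods at January 2021, so it fits poorly with a hypothesis about change over the whole pandemic course

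*Protocol article*

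**What the plan says.** Under Aims, objectives and hypotheses, a secondary hypothesis on patterns over time reads: "Mental health and well-being will follow the trajectory of the pandemic, with poorer outcomes evident during/after higher levels of COVID-19 prevalence". It carries no date limit. The Introduction also lists, as a distinct feature of the study, that longitudinal data will show whether symptoms that surge in a crisis last or resolve.

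The Analysis plan for the longitudinal cohort describes two sets of models.

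- **Three-wave models.** These are three-level random intercept models, "considering observations from baseline, 6-month follow-up and 12-month follow-up at level 2 and NHS trusts at level 3". The associations named for them are with staff and job characteristics.
- **Pressure analysis.** The text continues: "We will use a measure of pressure on Trusts as the key exposure". Pressure is plotted over time by Trust, "before partitioning the data into meaningful periods corresponding to burden level over the baseline data collection period (April 2020 to January 2021". Two steps follow: "We will plot all measures over time to look at patterns between this exposure and outcome levels", and then three-level models "to explore factors associated with outcomes in each period".

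Under Study procedures, Data collection: "Baseline data were collected from April 2020 to January 2021". Follow-up invitations are timed from each participant's own baseline, at 6 and 12 months.

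**The concern.** The trajectory hypothesis asks whether outcomes rise and fall with the burden of the pandemic. Three features of the pressure analysis make it a weak answer.

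1. **Window.** The burden periods end when baseline collection ends, yet follow-up continues for another year.
2. **Who is compared.** Each person gives one baseline response. Within the window, a contrast between periods is mostly a contrast between people who joined at different times, so burden is mixed with who chose, or was able, to answer then. The planned weights are raked within each Trust on age, sex, ethnicity and role. As described, they do not balance the respondent mix across calendar time.
3. **What is modelled.** A model of factors within a period shows which staff fare worse in that period. It does not estimate whether the outcome level moves with pressure.

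What is at stake is a largely cross-sectional answer to a longitudinal question, from a cohort that will hold repeated measures on the same people.

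**Working it through.** The document gives no sample size, power or precision for this analysis, so there is no figure to reproduce. The check is calendar arithmetic.

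**Inputs from the protocol.** Baseline runs from April 2020 (the abstract says late April) to January 2021. Follow-up is due at baseline + 6 and + 12 months. The burden window ends in January 2021.

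**Assumptions.** Each survey is answered when due; late answers would only move more of them outside the window. Enrolment pattern and follow-up response are not given, so they are varied.

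**Step 1: calendar of the waves.**
- 6-month surveys: about late October 2020 to July 2021.
- 12-month surveys: about late April 2021 to January 2022.
- Share of 12-month surveys inside the window: 0%.
- A 6-month survey is inside only if baseline + 6 months ≤ 31 January 2021, that is, baseline by about 31 July 2020.

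**Step 2: share F of 6-month surveys inside, under even enrolment.**
- Start 1 April 2020: 121 days to 31 July out of 305 days to 31 January, so F = 121/305 = 0.397.
- Start 24 April 2020: F = 98/282 = 0.348.

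**Step 3: share of all follow-up surveys outside.** With response proportions r6 and r12, the share outside is 1 − F × r6/(r6 + r12).

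| Enrolled by end July 2020 (F) | r6 = r12 | r6 = 0.6, r12 = 0.4 |
|---|---|---|
| 0.348 (even, 24 April start) | 82.6% | 79.1% |
| 0.397 (even, 1 April start) | 80.2% | 76.2% |
| 0.50 | 75.0% | 70.0% |
| 0.75 | 62.5% | 55.0% |
| 0.90 | 55.0% | 46.0% |
| 1.00 (limiting case) | 50.0% | 40.0% |

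**Step 4: who supplies two responses inside the window.** Only people enrolled by about end July 2020 can. Everyone enrolled later contributes a baseline response alone. A person's surveys are about six months apart, so any continuous burden period shorter than that holds at most one response per person. If separate linear models were fitted to such periods, between-person variance could not be told apart from residual variance.

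**Step 5: where pressure meets outcome level.** Reading the Analysis plan in order, the three-wave models are stated for staff and job characteristics, the period models are stated for factors within a period, and the plots are the one step that explicitly sets pressure beside outcome level.

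**The case against.** The strongest reply is that the article is condensed and the pressure analysis exploratory. The objective is secondary and descriptive, and the verbs are of plotting and exploring. Details such as lags or random-effect structure belong in an analysis plan that is not shown. That stands for those details. It does not cover the window, which is a dated restriction and not an omission.

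Several stronger readings are tempting, and the text does not support them.

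- **Most follow-up data go unused.** Not by the plan as a whole: the three-wave models use every wave, and the plots have no stated end date. The point applies only to the burden-period analysis. Even there, the share outside depends on enrolment figures that are not given.
- **The periods contain entirely different people.** The plan partitions the data, not baseline responses alone, and early joiners are due a 6-month survey inside the window.
- **The models must be separate for each period.** The wording "use three-level random intercept logistic and linear regression models, as appropriate, to explore factors associated with outcomes in each period" reads most naturally that way, but one model with period terms is not excluded. The identifiability remark in the working depends on the separate-model reading.
- **Pressure can never be tested against outcome.** The sentence naming it as main exposure directly follows the three-wave models and could be read as applying to them. The text does not say so clearly.
- **A within-person contrast would halve the variance.** This follows from an assumed within-person correlation of 0.5, but it compares n people with 2n and ignores that exposure is aggregated over 18 Trusts. The documents support no such precision figure.

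Overlap between late baselines and early 6-month surveys is no fault either. It is a reason to use calendar periods, as the plan does.

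**Conclusion.** The point holds as a mismatch between window, model and hypothesis. The burden periods cover April 2020 to January 2021, while the hypothesis concerns change over time without that limit. It follows from the stated dates, with no assumption about enrolment, that every 12-month survey and the 6-month surveys of everyone enrolled after about July 2020 lie outside the periods. The overall share of follow-up outside does rest on assumptions: about 80–83% with even enrolment and equal response, 55–75% if 50–90% enrolled by end July, and half or less only if nearly everyone enrolled by then, or if about 90% did and 12-month response was clearly lower. Period contrasts mainly compare different respondents, and a plot is the only clearly stated link between pressure and outcome level. This weakens one secondary hypothesis. It does not undermine the prevalence estimates or the three-wave analysis of staff and job characteristics.

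**What to change.** Extend the Trust pressure series and the burden periods to the end of 12-month follow-up, about January 2022. Link each response, at every wave, to its Trust's pressure at the calendar date of response. Enter pressure as a time-varying covariate in the three-wave model already planned, with the structure written as occasions within participants within Trusts. Replace per-period models with factor-by-burden interactions in that model, and keep the plots as description.

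If the exposure data cannot be extended, limit the trajectory hypothesis to the baseline window and report the result as largely cross-sectional.

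The cost is about 12 more months of Trust-level bed and staffing data, whose availability the protocol does not state, plus changed wording and some added analysis. No new participant data are needed.
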